#### Baseline Assessment

Prior to the first treatment, both the patient and legal guardian will be asked to provide demographic and socioeconomic information (SES) including: age, race, ethnicity, gender, annual household income range, patient occupation (from those who work), guardian occupations and specific insurance coverage status. We will also collect a complete medical history of pilonidal disease, family history of pilonidal disease, current pilonidal disease symptoms, current hygiene regime, and history of physician office visits, Emergency Department/urgent care visits and inpatient hospitalizations for pilonidal disease.

The child and legal guardian will be asked to complete the age appropriate PedsQLTM Quality of Life Inventory and questions about healthcare associated disability, pain and pilonidal disease management. The patient will also complete the Child Attitude Toward Illness Scale (CATIS) and the parent and child will complete the disease-related stigma scales. To assist with the costs and time spent participating in the study, parking

484 costs will be paid for by the study and a \$20 research debit card will be  
485 given to the patient or their legal guardian at the end of the visit.

486 **Immediately Following/ 24hrs Post-Treatment (Intervention Group)**

487 Immediately following each laser treatment and 24 hours after, the patient  
488 will be asked to rate their pain from 1-10 utilizing the Numeric Rating  
489 Scale (NRS-11) (see Appendix for Pain Scale). Contact for the 24 hour  
490 follow-up will be completed by phone, text or email.

491 **Follow-up at 1, 2, 3, and 4 months**

492 The patient and legal guardian will complete surveys assessing healthcare  
493 associated disability, pain, pilonidal disease management, and Emergency  
494 Department/ urgent care/ physician office/hospital visits that occurred  
495 between follow-up assessments. In addition, the CATIS will be completed  
496 at the 2 month follow-up, the parent and child disease-related stigma  
497 scales will be completed at the 3 month follow-up, and the age appropriate  
498 Child and Parent PedsQLTM will be administered at the 4 month follow-  
499 up. The Healthcare Satisfaction questionnaire will be administered at the 1  
500 and 4 month follow-ups. These surveys and questionnaires will be  
501 completed at the in-person visits for patients in the laser group and by  

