502 either phone or email/web-based survey for patients in the control group  
503 (unless they scheduled an in-person visit for any of these follow-ups, in  
504 which case they will be completed at the in-person visit). To assist with  
505 the costs and time spent participating in the study, a \$20 research debit  
506 card will be given to the patient or their legal guardian at the end of the  
507 visit or mailed to the legal guardian's address (or patient's address if 18  
508 years of age or older) upon successful completion of the surveys.

509 Subjects who will turn 18 before their 1, 2, 3, and 4 month follow-ups will  
510 be asked to sign the informed consent used for the study and to update  
511 their contact information. After speaking with the subject and explaining  
512 the study, an informed consent and contact information sheet will be  
513 mailed to the subjects to sign so that we may continue to collect data up to  
514 24 months after their initial study treatment.

515 **Post-Treatment Follow-Ups at 6, 9, 12, 18, and 24 months**

516 Each subject will receive an email or telephone call at 6, 9, 12, 18, and 24  
517 months after their initial visit. Follow-up will be conducted by email/web-  
518 based survey or by phone with a member of the research team from NCH.  
519 The patient and legal guardian will complete surveys assessing healthcare  
520 associated disability, pain, pilonidal disease management, and Emergency  
521 Department/ urgent care/ physician office/hospital visits that occurred  
522 between follow-up assessments. At 6 and 12 months, the age appropriate

PROTOCOL TITLE: A randomized controlled trial of laser hair depilation in adolescents with pilonidal disease

523 Child and Parent PedsQLTM and the CATIS will be administered. At 9  
524 months, healthcare satisfaction and disease related stigma scales will be  
525 administered. A \$20 research debit card will be mailed to the legal  
526 guardian's address (or patient's address if  $\geq 18$  years of age) upon  
527 successful completion of the surveys at 6 and 9 months. A \$50 research  
528 debit card will be mailed the legal guardian's address (or patient's address  
529 if  $\geq 18$  years of age) upon successful completion of the surveys at 12  
530 months.

531 At the 12 month time point, patients randomized to the control group will  
532 be offered laser treatment, at no cost, contingent on the interim analyses of  

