#### **COVID-19 additional surveys**

Patients whose treatments are delayed, may still complete the 1, 2, 3, and 4 month follow up surveys without being seen for their laser treatments. When the non-essential visits open back up, patients will complete the rest of their treatments and complete the corresponding visit surveys. Since these are additional surveys that were not a part of the original consent, the patient will be asked to voluntarily sign an addendum demonstrating their willingness to complete the surveys. These additional surveys will replicate the corresponding visit surveys previously mentioned. To assist with the costs and time spent participating in the study, a \$20 research debit card will be given to the patient or their legal guardian at the end of the visit or mailed to the legal guardian's address (or patient's address if 18 years of age or older) upon successful completion of the surveys.

6.5 If there are plans for long-term follow-up (once all research related procedures are complete), what data will be collected during this period.  
N/A

6.6 For Humanitarian Use Device (HUD) uses provide a description of the device, a summary of how you propose to use the device, including a description of any screening procedures, the HUD procedure, and any patient follow-up visits, tests or procedures. N/A

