## 1117 **19.0 Provisions to Protect the Privacy Interests of Subjects**

1118 19.1 Study members will only contact participants a maximum of three  
1119 times for recruitment and follow up surveys. Please see section 13 for  
1120 additional information.

1121 19.2 The patient is informed from the beginning that participation is  
1122 voluntary and they may withdraw at any time. They also are not required  
1123 to answer any survey question that they do not want to. This is laid out  
1124 clearly in the consent form.

1125 19.3 Sources for data collection will be the patients' electronic health  
1126 record (EPIC) and REDCap surveys that will be stored in the REDCap  
1127 database.

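### At months 1 to 4 the secondary questionnaires are answered in clinic by the laser arm and remotely by default in the control arm, so survey mode is largely, though not completely, confounded with treatment

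*Combined protocol and SAP*

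**What the plan says.** Section 6.4, under the heading for follow-up at 1, 2, 3 and 4 months, says that the surveys and questionnaires are "completed at the in-person visits for patients in the laser group and by" "either phone or email/web-based survey for patients in the control group". Controls have an exception: "unless they scheduled an in-person visit for any of these follow-ups, in" which case they answer at that visit. Laser patients have one too. Under the COVID-19 subsection, those whose treatment is delayed "may still complete the 1, 2, 3, and 4 month follow up surveys without being seen for their laser treatments".

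The same part of 6.4 places CATIS at month 2, the stigma scales at month 3 and healthcare satisfaction at months 1 and 4. For quality of life, "Child and Parent PedsQLTM will be administered at the 4 month follow"-up, whereas Table 2 marks month 3. The pain and pilonidal-management items are asked every month.

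From month 6 the two arms are followed alike: "Each subject will receive an email or telephone call at 6, 9, 12, 18, and 24" months, with answers given by web survey or phone.

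Four other places bear on this:
- Section 6.2 (control group) discusses the control arm's fewer in-person visits and concludes that monthly phone or email contact keeps data collection similar. It does not discuss survey mode.
- Section 4.1 lists quality of life, satisfaction, attitudes and stigma as secondary outcomes without a time point.
- Section 17.1 compares other outcomes by chi-square, t or Mann-Whitney tests, with no mode term or sensitivity analysis.
- Section 17.2 states that participants and staff know the allocation.

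**The concern.** Laser families answer at a treatment visit, with the treating team present. Control families answer away from the clinic unless they book a visit. The questions are subjective: rating the staff, embarrassment and secrecy, feelings about the illness, pain, and whether the recommended hair removal was done. Answers to such questions may depend on whether they are given face to face, by phone or alone online, and on who is nearby. The laser arm answers the hair-removal item at visits where section 6.2 has supplies and instruction handed out.

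Any effect of mode or setting would enter the between-arm difference and look like an effect of laser. Because section 4.1 names no time point for these scales, a month 1 to 4 difference could be reported as a secondary result. Satisfaction is the most exposed: it has no baseline, and two of its three assessments fall in this window.

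**Working it through.** **Step 1. Which assessments are affected (section 6.4 and Table 2).**

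| Scale | Baseline | Months 1–4 (mode differs by arm) | Month 6 on (remote in both arms) |
|---|---|---|---|
| Satisfaction | none | 1, 4 | 9 |
| CATIS | yes | 2 | 6, 12 |
| Stigma | yes | 3 | 9 |
| PedsQL | yes | 4 (Table 2: 3) | 6, 12 |
| Pain and hair-removal items | yes | 1, 2, 3, 4 | 6, 9, 12, 18, 24 |

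PedsQL lies in the affected window whichever month is right.

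**Step 2. Sample size for the illustration.** Sections 12.1 and 17.1 give 12% against 2%, two-sided 5%, 80% power and 122 per arm. The two-proportion formula with pooled variance under the null gives

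[1.960·√(2·0.07·0.93) + 0.842·√(0.12·0.88 + 0.02·0.98)]² / 0.10² = 101.0, so 102.

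The continuity correction, (101.0/4)·[1 + √(1 + 4/(101.0·0.10))]², gives 120.2, so 121 against the stated 122. An O'Brien-Fleming-type look at 25% information spends about 0.0001 of alpha and changes almost nothing. Dropout: 122/0.9 = 135.6, so 136, as stated. The plan's figure reproduces.

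After the increase to 151 per arm, section 12.1 explains that about 15 laser patients gave no data. The expected evaluable laser arm is then (151 − 15) × 0.9 = 122.4, so 122 is the figure to use.

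**Step 3. Effect of an assumed mode shift on a mean score.** The documents give no mode effect, no scale SD and no share of controls seen in person. Let d be the shift in SD units from in-clinic completion and f the share of controls who answer in person. With no true treatment effect and n per arm,

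δ = d(1 − f)·√(n/2), and P(significant) = Φ(δ − 1.96) + Φ(−δ − 1.96).

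For n = 122, √(122/2) = 7.81. Example: d = 0.2 and f = 0 give δ = 1.562 and P = Φ(−0.398) + Φ(−3.522) = 0.346.

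| Assumed d | f = 0 | f = 30% |
|---|---|---|
| 0 (same mode) | 5.0% | 5.0% |
| 0.1 SD | 12.2% | 8.5% |
| 0.2 SD | 34.6% | 19.4% |
| 0.3 SD | 64.9% | 37.5% |

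For scale, at 122 per arm an observed difference of 1.96·√(2/122) = 0.25 SD is significant, and (1.96 + 0.842)·√(2/122) = 0.36 SD is detected with 80% power. A shift within the assumed range is thus comparable with the effects the trial could detect on these scales.

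**The case against.** The best defence is that the design already contains most of the problem. Every affected scale is repeated at month 6 or later, by web or phone in both arms. Change from an in-clinic baseline to those times carries the same change of mode in each arm, apart from any baseline not taken in clinic, since section 13.1 allows telehealth enrolment. The sponsor also considered the unequal visits in section 6.2 and had practical reasons for not bringing controls in monthly. This stands, and it limits the point to months 1 to 4. It does not settle it, because section 6.2 says nothing about survey mode and the plan does not prefer the later assessments.

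A reader might infer that mode coincides exactly with arm, so that nothing can be done in analysis. The documents do not support that. Controls may book visits, and COVID-delayed laser patients may answer without being seen, so there is overlap of unknown size in both directions. The overlap arises from choice or circumstance, and section 6.4 does not ask for the mode to be recorded, so adjustment would be weak, but not impossible in principle.

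A reader might also take 151 × 0.9 = 136 evaluable per arm, which gives 13%, 38% and 70% when f = 0. That overlooks the 15 or so laser patients without data. With 122 laser and 136 control patients the 0.2 SD figure is about 36%, close to the 35% used here.

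It is also fair to say that the size of the effect is wholly assumed, and that the later assessments mix phone and web. The mix is open to both arms on the same terms, unlike the month 1 to 4 split, but it is a reason to record mode throughout.

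**Conclusion.** The difference in survey mode at months 1 to 4 is explicit in section 6.4, and nothing in section 17.1 deals with it. Mode and setting are largely, not completely, confounded with arm for satisfaction, CATIS, stigma, PedsQL and the monthly pain and hair-removal items. The consequence is less certain than the difference. If in-clinic completion shifts mean scores by 0.1 to 0.3 SD, the chance of a spurious significant result rises from 5% to between 12% and 65% with no controls in person, or between 8.5% and 38% with 30% in person. Both the shift and the 30% are assumptions, and the direction of any shift is unknown.

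These figures are for mean scores. They do not cover compliance, which section 4.1 defines as rates and which comes from categorical items; the mode concern applies to it, but no size is given here.

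A reader might go on to infer that one-year recurrence is biased as well, or that the sample size is wrong. Neither follows: event detection is a separate question from how attitude and satisfaction scales are answered, and the sample size does not depend on these scales. This is an inexpensive improvement to secondary analyses that is worth making; it does not threaten the main result.

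**What to change.** **Section 6.4.** For months 1 to 4, have both arms complete the scales on the same self-completed REDCap form. Laser families use a link before the visit, or a tablet before they see staff and before the laser session. Phone is the fallback in both arms. Record the mode of every survey, including those at month 6 and later. State one month for PedsQL in the text and Table 2.

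**Section 17.1.** Name the remotely collected assessments as the main between-arm comparisons: PedsQL and CATIS at 6 and 12 months, satisfaction and stigma at 9 months. Report month 1 to 4 contrasts as descriptive, with the mode stated.

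**Cost.** No visits are added. Section 19.3 already lists the electronic health "record (EPIC) and REDCap surveys that will be stored in the REDCap" database as data sources, and the COVID-19 subsection already lets some laser patients answer without a treatment visit. There are two downsides. Early data carry less weight. And with this version dated February 2021 and enrolment due to end in September 2021, the change reaches only surveys not yet collected, so mode will change partway through the laser arm. The section 17.1 change needs no new data and also covers patients already surveyed.

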533 adverse events for this study. If these patients choose to receive the  
534 elective laser treatments, they will be brought back into the clinic and re-  
535 consented by the study staff prior to their first treatment. They will have  
536 the option to commit to one or two additional years in the study and will  
537 be followed in the same manner as the patients initially randomized to the  
538 laser intervention group. Data will be collected from the patients per the  
539 same follow-up surveys at 1, 2, 3, and 4 months and post-treatment  
540 follow-up surveys at 6, 9, 12, 18, and 24 months after their initial visit. A  
541 \$20 research debit card will be mailed to the legal guardian's address (or  
542 patient's address if  $\geq 18$  years of age) upon successful completion of the  
543 surveys at 6 and 9 months. A \$50 research debit card will be mailed the  
544 legal guardian's address (or patient's address if  $\geq 18$  years of age) upon  
545 successful completion of the surveys at 12 months. Since laser therapy has  
546 previously been shown to be safe and tolerable, patients and caregivers in  
547 the control group will be informed of the safety monitoring data and the  
548 recurrence rates from the interim analysis when available (Analysis  
549 section above) and allowed to decide if they would like to receive laser  
550 therapy.

551 Subjects who will turn 18 before their 12, 18, or 24 month follow-up will  
552 be asked to sign the informed consent used for the study and to update  
553 their contact information. After speaking with the subject and explaining  
554 the study, an informed consent and contact information sheet will be  
555 mailed to the subjects to sign so that we may continue to collect data up to  
556 24 months after their initial study treatment.

557 **6 months post 1st treatment ( $\pm 30$  days)**

558 A member of the research team from NCH will contact the family over the  
559 phone or email and ask questions about any problems the child has had  
560 with their pilonidal disease since their 30-day follow-up. Specifically, we  
561 will ask about subsequent ED/Urgent Care visits or physician visits,  
562 readmissions and operations, additional imaging, and missed days from  
563 normal activities by the patient and legal guardian that were related to  
564 their pilonidal disease. We will also ask about the out-of-pocket

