PROTOCOL TITLE: A randomized controlled trial of laser hair depilation in adolescents with pilonidal disease

565 expenditures directly spent on post-treatment medical care and returning  
566 visits (e.g. insurance copayments; costs of drugs) and other expenditures  
567 related to the visits (e.g. transportation costs) within one year. Please see  
568 the form in the appendix for data points to be collected during this phone  
569 call.

570 For subjects who will turn 18 before their 6-month follow-up, they will be  
571 asked to sign the informed consent used for the study and to update their  
572 contact information. After speaking with the subject and explaining the  
573 study, an informed consent and contact information sheet will be mailed to  
574 the subjects to sign so that we may continue to collect data up to 24  
575 months after their initial study treatment.

576 A \$20 research debit card will be mailed to the legal guardian's address  
577 upon successful completion of the survey.

578 **9 months (±30 days)**

579 A member of the research team from NCH will call or email the family  
580 and ask questions about any problems the child has had with their  
581 pilonidal disease since their six-month follow-up. Specifically, we will ask  
582 about subsequent ED/Urgent Care visits or physician visits, readmissions  
583 and operations, additional imaging, and missed days from normal  
584 activities by the patient and legal guardian that were related to their  
585 pilonidal disease. We will also ask about the out-of-pocket expenditures  
586 directly spent on post-treatment medical care and returning visits (e.g.  
587 insurance copayments; costs of drugs) and other expenditures related to  
588 the visits (e.g. transportation costs) within one year. Please see the form in  
589 the appendix for data points to be collected during this phone call.

590 For subjects who will turn 18 before their 9-month follow-up, they will be  
591 asked to sign the informed consent used for the study and to update their  
592 contact information. After speaking with the subject and explaining the  
593 study, an informed consent and contact information sheet will be mailed to  
594 the subjects to sign so that we may continue to collect data up to 24  
595 months after their initial study treatment.

596 A \$20 research debit card will be mailed to the legal guardian's address  
597 upon successful completion of the survey.

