630 provide an additional consent at the time that they begin to receive laser  
631 treatments.

632 \* If at the 12 month time point, the subject treated with the laser feel that  
633 they have significant hair re-growth, they will be asked if they would like  
634 to be re-evaluated for further laser hair removal at no cost.

635 **18 and 24 months post 1st treatment (±30 days)**

636 A member of the research team from NCH will call or email the family  
637 and ask questions about any problems the child has had with their  
638 pilonidal disease since their 12 or 24-month follow-up. Specifically, we  
639 will ask about subsequent ED/Urgent Care visits or physician visits,  
640 readmissions and operations, additional imaging, and missed days from  
641 normal activities by the patient and legal guardian that were related to  
642 their pilonidal disease. We will also ask about the out-of-pocket

expenditures directly spent on post-treatment medical care and returning visits (e.g. insurance copayments; costs of drugs) and other expenditures related to the visits (e.g. transportation costs) within one year. Please see the form in the appendix for data points to be collected during this phone call.

For subjects who will turn 18 before their 12 or 24-month follow-up, they will be asked to sign the informed consent used for the study and to update their contact information. After speaking with the subject and explaining the study, an informed consent and contact information sheet will be mailed to the subjects to sign so that we may continue to collect data up to 24 months after their initial study treatment.

Participants will not be reimbursed for the 18 and 24 month follow-up time points.

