**Sample Study Data Collection Questionnaire: Pilonidal Management**

**(Child):**

The items below will be modified to reflect the appropriate time point in the study

For baseline: wording will be modified to say, in the last month...

For the treatment phase: wording will be modified to say, since you last treatment...

For the follow-up time points: wording will be modified to say, since your last follow-up...

1. In the last month, how many days did you experience pain due to your pilonidal disease?  
\_\_\_\_\_ number of days
2. When you experienced pain, can you tell me how severe the pain was on a scale from 1-10, 1 being no pain and 10 being terrible pain
3. On average, how long would your pain last?
  - a. Minutes
  - b. Hours
  - c. Days
  - d. The entire time, I am still in pain
4. Since your last treatment have you experienced any of the following symptoms?:
  - Swelling, redness, or sore skin in and around the treatment area yes/no  
If yes, did you see a doctor for these symptoms y/n  
If yes, please describe the instructions and treatments that the doctor provided
  - Pus or blood (drainage of pus or blood) in or around the treatment area yes/no  
If yes, did you see a doctor for these symptoms y/n  
If yes, please describe the instructions and treatments that the doctor provided
  - A bad odor coming from the treatment area yes/no  
If yes, did you see a doctor for these symptoms y/n  
If yes, please describe the instructions and treatments that the doctor provided
  - Holes or openings in or around the treatment area yes/no  
If yes, did you see a doctor for these symptoms y/n  
If yes, please describe the instructions and treatments that the doctor provided
5. Since your last treatment did you use nair or shaving for your pilonidal disease?
  - Yes, I used nair only
  - Yes, I used shaving only
  - Yes, I used both nair and shaving
  - No, I did not use either
6. Since your last treatment how often have you used nair (branch from 1 or 3)?
  - More than 1 time per week
  - 1 time per week
  - At least 2 times since the last treatment
  - At least 1 time since the last treatment
  - I did not use the nair at all since my last treatment
7. Did someone help you with applying the nair to the treatment area?
  - Yes
  - No
8. Since your last treatment how often have you shaved (branch from 2 or 3)?

PROTOCOL TITLE: A randomized controlled trial of laser hair depilation in adolescents with pilonidal disease

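### The 6-month interview recalls back to the 30-day follow-up, re-covering months already surveyed, and no rule says how overlapping reports enter the 1-year totals of disability days, visits and costs

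*Combined protocol and SAP*

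**What the plan says.** All references are to the combined protocol and SAP.

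- **Months 1 to 4 (Section 6.4).** Both arms complete surveys on disability, pain, disease management and health-care visits that took place "between follow-up assessments. In addition, the CATIS will be completed". The second sentence in that quote opens the questionnaire schedule and is not at issue.
- **Months 6 to 24, general text (Section 6.4, post-treatment follow-ups).** The same content is collected for visits "between follow-up assessments. At 6 and 12 months, the age appropriate", so the 6-month window would start at month 4.
- **6-month interview (Section 6.4, own subheading).** Families are asked about problems "with their pilonidal disease since their 30-day follow-up". The items include "readmissions and operations, additional imaging, and missed days from" normal activities, for patient and guardian.
- **9- and 12-month interviews.** Each counts from the contact before it.
- **18- and 24-month interviews.** The anchor is "pilonidal disease since their 12 or 24-month follow-up".
- **Costs.** The interviews at 6, 9, 12 and 18/24 months each ask for out-of-pocket spending and for other expenditure "related to the visits (e.g. transportation costs) within one year".
- **Sample child questionnaire (Appendix).** "For the follow-up time points: wording will be modified to say, since your last follow-up". Treatment-phase items count from the last treatment.
- **COVID-19 additional surveys (Section 6.4).** Patients with delayed treatments may complete the 1- to 4-month surveys on schedule, then complete visit surveys when treatment resumes. "These additional surveys will replicate the corresponding visit surveys previously mentioned". They are voluntary and need a signed addendum.
- **Analysis (Section 17.1).** Only the between-arm tests are named for these outcomes.

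**The concern.** Patient and caregiver disability days at 1 year are the first secondary outcomes named in Section 4.1. Table 2 adds emergency visits, readmissions, procedures, health-care costs and incremental cost-effectiveness at 12 months. Totals for the year have to be assembled from interval reports, so the intervals must tile the year without overlap, or a rule must remove what is reported twice.

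One year-1 window does not tile as written, the cost period is undefined, and one arm can supply extra reports. The plan gives no assembly rule. The doubly covered months also fall where laser patients attend for treatment (five sessions at 4- to 6-week intervals, so 16 to 24 weeks from first to last). Early treatment burden could therefore be weighted twice and later benefit once.

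**Working it through.** The plan gives no figure for 1-year days, visits or costs, so there is nothing to reproduce. The check counts months of recall within months 0 to 12, assuming a constant event rate and simple summing of reports. The 30-day follow-up is taken to be the 1-month contact, the only one in the schedule that fits.

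**1. Event windows, both arms**

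| Contact | Counting from previous contact | 6-month interview as worded |
|---|---|---|
| Months 1, 2, 3, 4 | 4 months | 4 months |
| Month 6 | 2 (months 4–6) | 5 (months 1–6) |
| Month 9 | 3 | 3 |
| Month 12 | 3 | 3 |
| Total | 12 | 15 |

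Excess = 15/12 − 1 = 25%. Months 1 to 4 (3 months) are the part covered twice.

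**2. Effect on the arm comparison**

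Let Δ be the true between-arm difference over the year and Δ(1–4) the part arising in months 1 to 4. The summed difference is Δ + Δ(1–4).

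- Events even over time in both arms: Δ(1–4) = 0.25Δ. The absolute difference grows by 25% and the ratio between arms is unchanged.
- Events clustered: the shift equals whatever difference arises in months 1 to 4. As an illustration with assumed figures, if laser adds 2 days in months 1 to 4 and saves 3 days later, the true difference is 2 − 3 = −1 and the summed difference is 2 + 2 − 3 = +1.

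**3. COVID repeat surveys, laser arm only**

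Assumptions: *d* treatments done before the pause (1 to 4), a gap of *g* months before the next (2 to 6), monthly treatments after that, all scheduled surveys completed, and resumed-visit surveys counting from the last treatment as in the sample questionnaire.

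Extra recall months = *g* + (4 − *d*).

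- Smallest (*d* = 4, *g* = 2): 2 + 0 = 2 months, 2/12 = 17%.
- Largest (*d* = 1, *g* = 6): 6 + 3 = 9 months, 9/12 = 75%.
- With the 15-month coverage above: (15 + 2)/12 − 1 = 42% to (15 + 9)/12 − 1 = 100%.

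The share of the laser arm affected is not given. If it were 5% to 30%, the laser-only excess in the arm mean would run from 0.05 × 2/12 = 0.8% to 0.30 × 9/12 = 22.5% of a 12-month total. With no repeats, or with one report kept per interval, it is zero.

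**4. Costs**

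- Read as spending since the previous contact: no excess.
- Read as cumulative at 6, 9 and 12 months, and then summed: 6 + 9 + 12 = 27 months for 12, or 27/12 = 2.25 times.

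**5. After the fix**

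With every window counted from the last completed contact and each interval used once, recall is 12 months for 12 in both arms.

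**The case against.** The strongest reply is that a non-overlapping window already exists. The general follow-up text and the sample questionnaire both give it, the 9- and 12-month windows are correct, and the 30-day phrase may be a stray that never reached the instrument. That stands as far as it goes: this is a contradiction between passages, and the documents do not show which wording was used in the calls.

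A reader might infer that the 1-year totals *are* double-counted, partly in one arm. The documents do not support that, for these reasons:

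- No section says the interval reports are added without reconciliation.
- The 30-day wording applies to both arms; with even events it scales both equally.
- The COVID repeats are optional and cover only the remaining treatments. Patients whose first treatment was delayed had no data collected (Section 1.0). Eight reports against four for the 1- to 4-month visits is the extreme case, not the typical one.
- The 2.25-fold cost figure is one reading of an ambiguous phrase, which may only describe the costing horizon.
- The 18/24-month anchor looks like a slip and touches no 1-year outcome.

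Section 6.3 also allows record review, which can identify repeated visits. It helps less elsewhere. The sample form asks for a number of pain days without dates and shows no missed-day or cost item. Billing information is not marked among the health information to be accessed. Days and out-of-pocket costs reported twice would be hard to separate later.

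**Conclusion.** The concern holds as a contradiction in the collection rule, together with a missing rule for building totals. Followed as worded and summed, the 6-month interview gives 15 months of recall for 12: +25% in both arms if events are even, and a distorted arm difference if days cluster in the laser treatment phase. The size of any clustering is not known.

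The only arm-specific source is the COVID repeats. They add 2 to 9 recall months per affected laser patient under the stated assumptions, and about 1% to 23% of the arm's 12-month total if 5% to 30% are affected; that share is an assumption. The cost excess lies anywhere between none and 2.25-fold, depending on the reading.

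The effect is confined to secondary outcomes and cost-effectiveness. Recurrence within 1 year is a yes/no outcome and is not inflated when the same event is reported twice.

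**What to change.** 1. Word the 6-, 18- and 24-month windows and all cost items as *since your last completed follow-up*, in line with the general text of Section 6.4 and the Appendix. This is safer than a fixed 4-month anchor, which would lose events when the 4-month survey was missed and would be unclear when it was repeated late.
2. Prespecify in Section 17.1 that each calendar interval counts once in the 1-year totals of disability days, visits and costs, with one report per interval where COVID repeat surveys exist.
3. For data already collected, establish which 6-month and cost wording was used, remove repeat visits by date, and report how many laser patients supplied repeat surveys.

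The cost is small: changes to the interview script and analysis wording, plus a date check on existing records.
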